
## Appendix 2 Measurement of Lipid level and Vital Signs

### Measurement of Vital Signs

Blood pressure (BP) and heart rate (HR) should be measured at each visit. BP should continue to be measured in the same arm as in the parent study unless a concomitant condition favors the use of a different arm. The appropriate size cuff should be used.

The diastolic blood pressure (DBP) will be recorded as the pressure noted when sound disappears (Korotkoff Phase V). BP and HR measurements should be determined after the subject has been seated for at least 5 minutes. The subject’s pulse should be measured for 30 seconds and the number should be multiplied by 2 to obtain heart rate.

### Lipid Measurements

The baseline lipid measurements for the purpose of analysis will be the central laboratory screening and day 1 lipid measurement collected after a ≥ 9 hour fast and before receiving intervention. At each time points, calculated LDL-C concentration will be determined. In addition, at screening, day 1, week 6, and week 12 LDL-C will be measured by preparative ultracentrifugation by the central laboratory. Only the screening calculated LDL-C concentration will be reported to the site for the eligibility decision. For subjects who are rescreened, data from the first screening period will not be used for the analysis. Investigators, subjects, and the study team will be blinded to post-randomization central laboratory lipid panel values for the duration of the study until unblinding of the database. In addition, investigators and staff involved with this trial and all medical staff involved in the subject’s medical care should refrain from obtaining lipid panels between randomization and at least 4 weeks after the subject ends the study at week 12 (to avoid potential unblinding). If a lipid panel is drawn, all reasonable steps must be undertaken to avoid informing the subject and study personnel of the results.

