### Trial design

This is a multicenter, open-label, randomized, stratified, active-controlled, noninferiority trial with two parallel groups. Randomization will be performed with a 1:1 allocation. Subjects with LDL-C values above the recommended level who meet the inclusion/exclusion criteria will be stratified based on their risk levels of heart disease [19, 20]. Then, they were instructed to follow the NCEP Adult Treatment Panel (ATP) [20] Therapeutic Lifestyle Change (TLC) diet first. After TLC is completed, subjects who have not reached the target lipid level will be randomly assigned to the treatments of either acupuncture and moxibustion or simvastatin. The duration of treatment for this study will be 12 weeks, followed by another 4 weeks for post-treatment assessment.

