### Outcome measurements

#### Primary outcome

The primary outcome is the percentage change from baseline to the end of the study (after the 12-week intervention and after another 4-week follow-up) in LDL-C. The calculated LDL-C concentration will be determined at screening (entry to the study), day 1 (after TLC is completed and eligibility is determined), week 6, and week 12. LDL-C will be measured by preparative ultracentrifugation by the central laboratory. The LDL-C concentration calculated at screening will be reported only for the eligibility decision. The baseline lipid measurements for the purpose of analysis will be the day-1 lipid measurement after TLC (lipid stabilization). This will be collected after a ≥9-h fast and before receiving intervention.

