#### TLC period

Subjects who complete the screening successfully and who meet the inclusion/exclusion criteria will initiate therapeutic lifestyle change (TLC). The TLC adherence report form is made and sent to subjects to monitor their lifestyle change process. Re-assessment will be conducted after the TLC period.

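### The analysis baseline for the primary endpoint is defined in two incompatible ways: day 1 after the diet phase in the main text, screening and day 1 in Appendix 2

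*Protocol article*

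**What the plan says.** The endpoint is a ratio to baseline: "The primary outcome is the percentage change from baseline to the end of the study" in LDL-C. The Primary outcome section then fixes that baseline: "The baseline lipid measurements for the purpose of analysis will be the day-1 lipid measurement after TLC (lipid stabilization"). It confines the screening value to another purpose: "The LDL-C concentration calculated at screening will be reported only for the eligibility decision".

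Appendix 2, under Lipid Measurements, opens its definition with the same words and ends it differently: "The baseline lipid measurements for the purpose of analysis will be the central laboratory screening and day 1 lipid measurement". It does not say whether the two values are averaged, used in turn, or used for different purposes.

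The order of events is clear. Under TLC period: "Subjects who complete the screening successfully and who meet the inclusion/exclusion criteria will initiate therapeutic lifestyle change (TLC"). Under Trial design: "After TLC is completed, subjects who have not reached the target lipid level will be randomly assigned". So screening is before the diet phase, day 1 is after it, and randomization follows the diet phase in both arms.

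The section Statistical analysis plan puts baseline LDL-C into the primary mixed model as a covariate, without further definition.

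LDL-C is obtained in two ways. Appendix 2 has a calculated value at each time point and adds: "at screening, day 1, week 6, and week 12 LDL-C will be measured by preparative ultracentrifugation by the central laboratory". Week 16 is not in that list, although the Primary outcome and Follow-up period sections place an efficacy assessment there.

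**The concern.** The same quantity is fixed twice, differently, in one document. This is not detail left for an analysis plan to supply, because both passages claim to state the baseline used for analysis. Two analysts following two sections would compute different values of the primary endpoint and fit different covariates.

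The Appendix 2 version brings in a value taken before the diet phase. Any fall in LDL-C during TLC would then appear as part of the change from baseline in each arm. The larger denominator would also scale down the difference between arms in percentage points. In a noninferiority comparison against a margin fixed in percentage points, a smaller difference with a proportionately smaller standard error makes noninferiority easier to conclude when the experimental arm is truly worse.

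**Working it through.** **1. The plan's own figure.** The Sample size section uses a difference of 0.343 and an SD of 0.7 on absolute LDL-C change, with power 0.80. Reading the significance level as two-sided 0.05: n per arm = 2 × [0.7 × (1.960 + 0.842) / 0.343]² = 65.4, against a stated figure of about 65. This reproduces. It does not involve the baseline definition, so it neither tests the point nor changes with the fix.

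**2. The two definitions side by side.**

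| | Primary outcome section | Appendix 2, Lipid Measurements |
|---|---|---|
| Values used as baseline | Day 1 only | Screening and day 1 |
| Position relative to TLC | After | One before, one after |
| Role of calculated screening value | Eligibility only | Eligibility report to the site; screening measurement also named as baseline |
| Combining rule | Not needed | None given |

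Both cannot hold.

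**3. Size if Appendix 2 is read as a mean.** The mean is one reading, assumed here. The documents give no TLC effect, so d, the proportional fall from screening to day 1, is assumed to be 5%, 10% or 15%. Set screening = 1 and day 1 = 1 − d. With a true proportional change c from day 1, the later value is (1 − d)(1 + c).

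- On the day-1 baseline the change is c.
- On the mean baseline, 1 − d/2, the change is f(1 + c) − 1, where f = (1 − d)/(1 − d/2).
- The between-arm difference is therefore multiplied by f.

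| Assumed d | f | Shrinkage | True 25% fall reads as | No change after day 1 reads as | True 10-point difference reads as |
|---|---|---|---|---|---|
| 5% | 0.95/0.975 = 0.974 | 2.6% | 26.9% | −2.6% | 9.74 |
| 10% | 0.90/0.95 = 0.947 | 5.3% | 28.9% | −5.3% | 9.47 |
| 15% | 0.85/0.925 = 0.919 | 8.1% | 31.1% | −8.1% | 9.19 |

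Screening alone, the outer limit of any weighting of the two values, gives a factor of 1 − d, or 9.0 points at d = 10%. Appendix 2 does not state that reading.

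**4. Check with baseline adjustment.** A simulation of 65 per arm with true changes of −30% and −20%, d = 10% on average, and a linear model adjusted for the chosen baseline gave a mean difference of 10.1 points on day 1, 9.5 on the mean and 9.1 on screening. Covariate adjustment does not undo the rescaling.

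**5. Illustrative consequence for the noninferiority test.** The article states no margin. Assume 10 points, with SD = 10 × 0.7/0.343 = 20.4 points and 65 per arm, so SE = 20.4 × √(2/65) = 3.58. With the true difference at the margin, the test statistic shifts by (10 − 10f)/(3.58f). At d = 10% this is 0.155; 1.960 − 0.155 = 1.805, an upper-tail probability of 3.6%. For d = 5%, 10% and 15%, the one-sided error of 2.5% becomes 3.0%, 3.6% and 4.3%.

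**6. Measurement method.** By Appendix 2, calculated LDL-C exists at every time point and ultracentrifuged LDL-C at screening, day 1, week 6 and week 12. A change to week 12 can be formed within either method. A change to week 16 can be formed within one method only if both values are calculated.

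**The case against.** **The main text is explicit, and Appendix 2 looks unadapted.** The appendix refers to a parent study and lists antibody and pharmacokinetic tests for AMG 145, which is not part of this trial. Its baseline sentence may be a remnant that nobody would follow. This makes harm less likely, but the sentence still stands as a definition of the analysis baseline, and the same appendix excludes first-screening data only for rescreened subjects, which suggests that screening data are otherwise used.

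**A reader might infer that the diet effect would be credited to acupuncture and moxibustion.** The documents do not support that. TLC precedes randomization for everyone, and efficacy is judged against the active control. Diet response enlarges the within-arm falls in both arms about equally. Only the rescaling of the difference remains.

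**A reader might infer that a day-1 baseline removes regression to the mean.** It does not. Only subjects still above target at the re-assessment after TLC are randomized, so the day-1 value also selects.

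**The appendix does not say the values are averaged.** This stands, and the figures above carry it as an assumption.

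**Two measurement methods are not a contradiction.** This also stands. Appendix 2 presents ultracentrifugation as additional to the calculated value, and naming the primary method is detail that an analysis plan commonly settles. Mixing methods at week 16 is avoidable, and the Dataset analysis section evaluates the primary endpoint at week 12.

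**Conclusion.** The contradiction is real and concerns the denominator and covariate of the primary analysis. As written, the primary endpoint has two definitions.

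Its numerical consequence is small. On the assumed mean reading and an assumed TLC effect of 5% to 15%, the between-arm difference in percentage change shrinks by 2.6% to 8.1%, or 0.26 to 0.81 points on a 10-point difference. The direction leans towards noninferiority when the experimental arm is worse; if the arms are truly equal, there is nothing to shrink. The error rates in the working rest on an assumed margin and show direction only. The between-arm difference in absolute LDL-C change, the scale on which the sample size was set, is not shifted.

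Nothing in the documents supports a claim that one arm is favoured by the diet phase itself, or that ultracentrifugation must be the primary method.

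**What to change.** Correct the baseline sentence in Appendix 2, Lipid Measurements, so that the analysis baseline is the day-1 LDL-C value only, taken after TLC and before the first intervention, as in the Primary outcome section. State that the same value is the covariate in the mixed model.

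As a secondary clarification, state that any given change in LDL-C uses one method at baseline and at every later visit. Because Appendix 2 lists ultracentrifugation only up to week 12, a change to week 16 should use calculated LDL-C at both day 1 and week 16. The visit list for calculated LDL-C in the Primary outcome section also ends at week 12, so week 16 should be added to agree with Appendix 2. Which method is primary is for the sponsor to choose and record before the data are unblinded.

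The cost is a few sentences. The day-1 measurements by both methods are already planned, Appendix 2 already provides for calculated LDL-C at every time point, and the sample size does not change.

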### Laboratory Assessments

All screening and on-study laboratory samples will be processed and sent to the central laboratory.

The central laboratory will provide a study manual that outlines handling, labeling, and shipping procedures for all blood samples. The date and time of sample collection will be recorded in the source documents at the site.

Table below outlines the specific analytic for serum chemistry, hematology, urinalysis, and other testing to be conducted.

**Table Taba:**

Chemistry	Coagulation	Urinalysis	Hematology	Other Labs
Sodium Potassium Chloride Bicarbonate Total protein Albumin Calcium Magnesium Phosphorus Glucose (Fasting) BUN or Urea Creatinine Uric acid Total bilirubin Direct bilirubin CK ALP LDH AST (SGOT) ALT (SGPT)	PT/INR	Specific gravity pH Blood Protein Glucose Bilirubin WBC RBC Epithelial cells Bacteria Casts Crystals	Hemoglobin Hematocrit MCV MCH MCHC RDW Platelets WBC Differential • Neutrophils • Bands • Eosinophils • Basophils • Lymphocytes • Monocytes	Fasting lipids • Total cholesterol • HDL-C • LDL-C • Triglycerides • VLDL-C ApoA1 ApoB hsCRP Lp(a) Anti-AMG 145 antibodies PK • AMG 145 • PCSK9 HbA1c FSH (if needed per exclusion 4.2.17) TSH eGFR (calculated) Fasting Vitamin E

## Abbreviations

AE: Adverse event
AHA: American Heart Association
ALP: Alkaline phosphatase
ALT: Alanine aminotransferase
AMH: Acupuncture and Moxibustion for Hyperlipidemia
ANCOVA: Analysis of covariance
ApoA1: Apolipoprotein A-1
ApoB: Apolipoprotein B
AST: Aspartate aminotransferase
BL: Bladder meridian
BP: Blood pressure
CABG: Coronary artery bypass graft
CAS: Complete analysis set
CHD: Coronary heart disease
CI: Confidence interval
CK: Creatine kinase
CVD: Cardiovascular disease
DBP: Diastolic blood pressure
DHA: Docosahexaenoic acid
DMC: Data monitoring committee
ECG: Electrocardiogram
EDAS: Effect durability analysis set
eGFR: Estimated glomerular filtration rate
EPA: Eicosapentaenoic acid
FAS: Full analysis set
HDL-C: High density lipoprotein cholesterol
HR: Heart Rate
hsCRP: High sensitivity C-reactive protein
IEC/IRB: Independent Ethics Committee/Institutional Review Board
LDH: Lactate dehydrogenase
LDL-C: Low-density lipoprotein cholesterol
LLN: Lower limit of normal
LOCF: Last observation carried forward
Lp(a): Lipoprotein(a)
NCEP ATP III: National Cholesterol Education Program Adult Treatment Panel III
NYHA: New York Heart Failure Association
PC: Pericardian meridian
PCI: Percutaneous coronary intervention
PPAR: Peroxisome Proliferator-Activated Receptor
RBC: Red blood cells
RCT: Randomized Controlled Trial
RN: Ren meridian
RR: Relative Risk
RRR: RR reductions
SAE: Serious adverse event
SBP: Systolic blood pressure
SP: Spleen meridian
ST: Stomach meridian
TC: Total cholesterol
TCM: Traditional Chinese Medicine
TG: Triglycerides
TLC: Therapeutic Lifestyle Change
TLR: Toll-like receptor
TLR4: Toll-like receptor 4
TSH: Thyroid Stimulating Hormone
ULN: Upper limit of normal
VLDL-C: Very low-density lipoprotein cholesterol
WBC: White blood cell
